#### Statistical methods

An initial overview analysis will be carried out to detect any errors and to check the data for normality (Shapiro-Wilks test), this being done for all participants and intervention groups.

Intention-to-treat (ITT) analysis will be performed for all recruited participants who complete the baseline assessment, regardless of whether they subsequently complete the whole protocol. Missing outcome values will be replaced by data registered in the previous assessment using the last observation carried forward (LOCF) technique.

For the baseline comparison of groups we will use the chi-square test (or Fisher’s exact test) for categorical data and the analysis of variance (ANOVA) (or Kruskall-Wallis test) for quantitative data (continuous or ordinal). If significant differences are detected we will use Student’s *t*-test (or Mann–Whitney test) for each pair of groups.

For the analysis of the *intervention* effect two time frameworks will be established: efficacy (at the end of the intervention: t1) and durability (at 24-week follow-up: t2). Change will be calculated as the change from baseline values, both as absolute values and as a percentage adjusted to baseline values. We will adjust repeated measures techniques to study the general behaviour of the outcomes in the follow-up.

Continuous variables will be expressed as mean and standard deviation (SD). Effect size will be estimated as the mean standardized difference between the mean of each group divided by the pooled standard deviation. In accordance with Cohen’s criterion [54], values of 0.2–0.5 represent small differences, 0.5–0.8 moderate differences and >0.8 large differences. Categorical variables will be expressed as counts (n) and percentages (%), unless otherwise specified.

All analyses will be conducted using the Statistical Package for the Social Sciences (SPSS) v17 (SPSS Institute Inc., IL, USA) and the level of significance will be set at *p* < 0.05.

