Secondary aims of the study are to investigate the effects of these interventions on systemic inflammation and adipose tissue function, cardiorespiratory fitness, physical activity and sedentary behaviour, dietary habits, empowerment related to health, self-efficacy in relation to physical activity and dietary habits, as well as the cost-effectiveness of the intervention with regard to health-related quality of life.

The study will also provide insights into the extent to which any observed changes persist in the medium term.

The general hypothesis is that among adults with risk factors for metabolic syndrome, those who participate in interventions designed to promote a healthy lifestyle through a combination of lifestyle counselling and supervised physical exercise of vigorous intensity will present greater improvements in terms of metabolic risk, physical condition, physical activity/sedentary behaviours and psychological parameters at the end of the intervention and at 24-week follow-up than will participants in interventions that combine lifestyle counselling with physical exercise of low-to-moderate intensity or those based exclusively on lifestyle counselling.

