#### Sample size

At least 105 individuals will be recruited for this study. Based on previous studies [20], a sample of this size would provide a beta risk of 0.2 and an alpha risk of 0.05 when using a bilateral contrast to detect a mean change in waist circumference of 6.0 cm (SD 5.3). Assuming a 20% drop-out rate at follow-up, we aim to recruit 35 individuals for each intervention group.

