### Data analysis

#### Timeline of data measurements

Measurements will be taken before (Baseline, t0 = 0 months) and after (t1 = 16 weeks) the intervention. As a medium-term follow-up measure, the two intervention groups and the control group will also be assessed 24 weeks after the end of the programme (t2).

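### LOCF credits participants lost between t1 and t2 with full retention of their gain and those lost before t1 with none, so the durability result can be biased, most plausibly towards persistence

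*Protocol article*

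**What the plan says.** All of the following is in the protocol article.

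- **Analysis set** (Statistical methods): "Intention-to-treat (ITT) analysis will be performed for all recruited participants who complete the baseline assessment", whether or not they finish the protocol. People without a t2 visit therefore stay in the t2 analysis.
- **Missing-data rule** (same section): "Missing outcome values will be replaced by data registered in the previous assessment using the last observation carried forward (LOCF) technique". No other rule or check is given.
- **Time frames** (same section): "efficacy (at the end of the intervention: t1) and durability (at 24-week follow-up: t2". Both are analysed as change: "Change will be calculated as the change from baseline values, both as absolute values and as a percentage adjusted to baseline values".
- **Visits** (Timeline of data measurements): baseline, t1 at 16 weeks, and t2, at which all three arms "will also be assessed 24 weeks after the end of the programme (t2".
- **Purpose of t2** (Background, after the secondary aims): "The study will also provide insights into the extent to which any observed changes persist in the medium term". The general hypothesis also covers the 24-week follow-up.
- **Expected loss** (Sample size): "Assuming a 20% drop-out rate at follow-up, we aim to recruit 35 individuals for each intervention group". How much falls before or after t1 is not stated.

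**The concern.** With only two visits after baseline, LOCF can do just two things.

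- **Lost between t1 and t2:** the t2 value is the t1 value. The participant is recorded as having kept all of the t1 change, so for that person the durability analysis assumes the quantity it should estimate.
- **Lost before t1:** the baseline value is carried to both visits. The participant is recorded as having no change at t1 or t2.

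Regression after week 16 is plausible. The supervised sessions end then, Risk and burdens names poor adherence as a main expected difficulty, and the Discussion treats unsupervised compliance as an open question. If most loss also falls in that period, the t2 result leans towards a lasting effect that may not exist.

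At t1 the rule shrinks each arm's gain in proportion to that arm's drop-out. If drop-out differed by arm, the t1 contrast would be distorted too.

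**Working it through.** **Inputs from the article:** 35 per arm, 20% drop-out at follow-up, waist circumference change of 6.0 cm with SD 5.3, two-sided alpha 0.05 (all from Sample size). The expected number missing per arm is 35 × 0.20 = 7.

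**Assumptions, not in the article:** 6.0 cm is read as a between-arm gap at t1 (the article calls it a mean change); the timing of loss; the share of benefit kept; a correlation of 0.7 between t1 and t2 changes. The plan gives no figure of its own for the effect of LOCF, so there is none to reproduce.

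**Bias in one arm's mean t2 change.** Let
- q = share missing at t2,
- B = mean t1 benefit,
- s = share of the missing who were lost after t1,
- r = share of B that the missing truly have at t2,
- c = share of B that completers have at t2.

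True mean = (1 − q)·c·B + q·r·B

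Mean under LOCF = (1 − q)·c·B + q·s·B

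Bias = q·B·(s − r)

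The sign is that of s − r. If q, s and r are the same in two arms, the bias in their contrast is the same expression with B replaced by the t1 gap.

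**Results with q = 0.20.** The false-positive rate at t2 comes from simulation (20,000 trials, t-test on LOCF values, comparator with no mean change) and applies only where the true t2 gap is zero.

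| t1 gap (cm) | True t2 gap (cm) | Loss after t1 | Bias (cm) | t2 false-positive rate |
|---|---|---|---|---|
| 6.0 | 0 | all | 0.2 × 6.0 × (1 − 0) = 1.2 | about 14% |
| 6.0 | 0 | half | 0.2 × 6.0 × (0.5 − 0) = 0.6 | 7 to 8% |
| 3.0 | 0 | all | 0.2 × 3.0 × (1 − 0) = 0.6 | about 7% |
| 3.0 | 0 | half | 0.2 × 3.0 × (0.5 − 0) = 0.3 | about 6% |
| 6.0 | 3.0 | all | 0.2 × 6.0 × (1 − 0.5) = 0.6 (3.6 reported) | – |
| 6.0 | 3.0 | half | 0.2 × 6.0 × (0.5 − 0.5) = 0 | – |
| 6.0 | 4.5 | half | 0.2 × 6.0 × (0.5 − 0.75) = −0.3 (4.2 reported) | – |

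With 10% missing, all after t1, a 6.0 cm gap and full relapse, the bias is 0.1 × 6.0 = 0.6 cm and the false-positive rate about 7%.

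**Unequal loss at t2 (assumed).** Suppose both arms gain 6 cm at t1 and relapse fully, and 10% of the exercise arm and 30% of the control arm are lost after t1. The contrast is then shifted by 0.1 × 6 − 0.3 × 6 = −1.2 cm, against exercise.

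**At t1.** With a share d lost before t1 who would have gained as much as the others, LOCF reports (1 − d)·B. Equal d shrinks both arms alike. For two arms that each truly lose 4 cm, with d of 30% and 10%, it gives 4 × 0.7 = 2.8 and 4 × 0.9 = 3.6 cm, a spurious 0.8 cm. That split is an illustration only.

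**The case against.** **The direction is not certain.** A reader might infer that everyone lost to follow-up is scored as having kept the full benefit, and hence that durability must be overstated. The article does not support this. Those lost before t1 count as zero change at t2, the split of the 20% is not given, and an individual session at weeks 18–19 (Table 1) is meant to agree plans against relapse. The last row of the table shows an understatement. This objection stands, and the point is limited accordingly.

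**The 14% is an extreme case.** It needs all loss after t1, complete relapse and a 6.0 cm gap between arms. All arms receive the counselling, so the control arm may improve too and the gap may be smaller. This also stands: 14% is the upper end of the zero-effect cases tabulated, not a forecast.

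**Standard errors.** A reader might add that treating filled-in values as observed makes the standard errors too small. For the simulated t2 contrast this does not hold. In the 6.0 cm, all-after-t1 case the mean model standard error is 1.32 against an empirical SD of 1.34, and with no effect at either visit rejection is about 5%. The inflation comes from the shifted mean.

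**Drop-out by arm.** The article expects poor adherence in general and says nothing of differences between arms, so distortion at t1 is a possibility only.

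**Other parts of the plan.** The section mentions repeated measures techniques, but not as an alternative to LOCF. They could mean a repeated-measures ANOVA, which needs complete records. A separate analysis plan might add sensitivity analyses, but the rule stated in the article would still be the wrong main rule.

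**Conclusion.** The concern holds in this limited form. The article fixes a single missing-data rule that, for anyone lost between t1 and t2, presupposes the answer to the durability question, and for anyone lost earlier presupposes no effect. The error therefore depends on when people leave and how much benefit they keep, neither of which the article gives. LOCF cannot be assumed conservative.

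In the tabulated 20%-missing cases the bias runs from −0.3 to +1.2 cm, with t2 false-positive rates of about 6 to 14% where the true t2 gap is zero. A shift towards persistence is the more plausible direction once supervision ends, but it is not established.

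This should be fixed before unblinded analysis. It weighs less than a fault in the main comparison would, because persistence is an additional question and efficacy at t1 is analysed separately.

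**What to change.** Replace the LOCF sentence with a likelihood-based mixed model for repeated measures on the observed t1 and t2 values, with baseline value, arm, visit and arm-by-visit terms and an unstructured covariance. Read the t1 and t2 arm contrasts from it, and state that it assumes data are missing at random. Participants with neither t1 nor t2 add little to this model, so report their number by arm.

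Keep two labelled sensitivity analyses: LOCF, and a version in which those lost after t1 return to baseline. Together they show how far the durability result depends on what is assumed about the missing.

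The cost is a change of wording and a little more analysis work. No visits, participants or measurements are added. The downsides are possibly somewhat wider intervals and reliance on missing at random, which the data cannot confirm.

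### The intervention effect is defined as change from baseline on two scales, with no baseline covariate stated and no rule on which scale decides

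*Protocol article*

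**What the plan says.** All of this is in the protocol article, Data analysis, Statistical methods. For the intervention effect, "two time frameworks will be established: efficacy (at the end of the intervention: t1) and durability (at 24-week follow-up: t2"). The next sentence defines the quantity: "Change will be calculated as the change from baseline values, both as absolute values and as a percentage adjusted to baseline values".

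Three other sentences in the section bear on baseline, and none makes it a covariate:

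- Longitudinal modelling: "We will adjust repeated measures techniques to study the general behaviour of the outcomes in the follow-up". How baseline enters is not stated.
- Baseline comparison of arms: "If significant differences are detected we will use Student’s" t-test or its rank equivalent for each pair of groups. Nothing follows from the result for the outcome analysis.
- Effect size: "Effect size will be estimated as the mean standardized difference between the mean of each group divided by the pooled standard deviation". As written, this is an unadjusted standardized difference.

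The analysis set is everyone with a baseline assessment, with missing outcomes filled by the last observation. Under Sample size: "Assuming a 20% drop-out rate at follow-up, we aim to recruit 35 individuals for each intervention group".

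**The concern.** A contrast of raw changes fixes the coefficient of baseline at 1. The best-fitting coefficient is ρ when variances are equal, so two things follow. The estimate has more variance than it needs, and when the arms happen to differ at baseline, part of that difference reappears in the estimated effect. With arms of 35, visible chance differences are likely on some outcome. The planned baseline significance tests may flag them, but no correction follows.

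The percentage version does not solve this. Dividing each change by the participant's own baseline is not covariate adjustment.

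The two versions can also disagree on significance. With no deciding scale, the conclusion can be chosen after the results are seen. At stake are precision that the collected data could supply for nothing, and an unambiguous answer per outcome.

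**Working it through.** **Inputs.** From Sample size: 35 per arm, 20% drop-out (35 × 0.8 = 28 completers), waist change 6.0 cm with SD 5.3 cm, two-sided α 0.05, β 0.2. From Statistical methods: all participants with a baseline assessment are analysed with carried-forward values, so about 35 per arm. Assumed, because the document gives no value: equal variance σ² at both visits, and ρ = 0.5, 0.7 or 0.9.

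**The plan's own figure.** The plan gives no precision figure for this analysis. Its sample size inputs give 2 × (1.96 + 0.84)² × (5.3/6.0)² = 12.2, so 13 per arm, and 13/0.8 = 16.25, so 17 after drop-out, against 35 stated. That mismatch is a separate matter. Only the planned 35 per arm is used below.

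**Precision.**
- Variance of a raw change: 2σ²(1 − ρ).
- Residual variance given baseline: σ²(1 − ρ²).
- Ratio, adjusted to raw: (1 − ρ²) / [2(1 − ρ)] = (1 + ρ)/2.

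**Chance imbalance.** The baseline difference D between two arms has standard error √(2/35) = 0.239 SD. Given D, the raw-change contrast is shifted by −(1 − ρ)D in expectation.

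| ρ (assumed) | Variance ratio | Variance cut | 35 / ratio | Share of D carried | Shift from a one-SE imbalance |
|---|---|---|---|---|---|
| 0.5 | 0.75 | 25% | 46.7 | 50% | 0.12 SD |
| 0.7 | 0.85 | 15% | 41.2 | 30% | 0.07 SD |
| 0.9 | 0.95 | 5% | 36.8 | 10% | 0.02 SD |

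**In centimetres of waist.** Take 5.3 cm as the SD of change. The difference detectable with 80% power at 35 per arm is 2.80 × 5.3 × √(2/35) = 3.55 cm. Multiplying by the square root of the ratio gives 3.07, 3.27 and 3.46 cm for ρ of 0.5, 0.7 and 0.9.

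**Two scales.** A simulation with 28 per arm and 4,000 runs per setting compared t-tests on absolute and on percentage change with ANCOVA on the untransformed follow-up value. Outcome distributions and effects are assumed.

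| Setting | Power: absolute / percentage / ANCOVA | Absolute and percentage disagree on significance |
|---|---|---|
| Waist-like (mean 100, true difference 4 cm), ρ 0.7 | 79.5 / 80.0 / 85.3% | 1.6% |
| Waist-like, ρ 0.9 | 78.0 / 78.3 / 79.3% | 3.0% |
| Triglyceride-like (log-normal, mean 150, SD 70, 27% reduction), ρ 0.5 on the log scale | 58.7 / 69.0 / 77.9% | 18.7% |
| Triglyceride-like, ρ 0.7 on the log scale | 79.8 / 90.1 / 91.6% | 12.8% |

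With no true effect and ρ 0.5, each triglyceride-like change test rejects in 5.2% of runs, and the two disagree in 3.8%. The chance that at least one rejects is therefore (5.2 + 5.2 + 3.8)/2 = 7.1%.

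**The case against.** **The text may not exclude adjustment.** The sentence defines derived variables and attaches no test to them. Absolute change modelled with baseline as covariate gives the same treatment estimate as ANCOVA on the follow-up value. The phrase about adjusting to baseline could loosely mean that. This stands in part: the wording is ambiguous, and under that reading the precision and imbalance points fall away for absolute change. But the phrase qualifies the percentage and most naturally means relative to baseline, and the question of which scale decides remains either way. The repeated-measures sentence does not settle it: if baseline is one of the repeated responses in a conventional analysis, the group-by-time contrast from baseline to one later visit is again the change-score contrast.

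**A reader might infer that the effect will be biased or the test invalid.** The documents do not support that. Expected regression to the mean is equal across randomized arms, the raw-change contrast is unbiased on average, and a single test keeps its size (5.2% in the simulation). Nor is every outcome selected beyond a threshold: Inclusion criteria ask for one or more of five factors, so many participants will not have qualified on any given one.

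**A reader might infer a material loss on every outcome.** The gain depends on ρ, which the document does not give. For waist, the outcome used for sizing, it is 5% of variance if ρ is 0.9.

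**Percentage change is not always the worse choice.** In the triglyceride-like simulation, where the effect was proportional, it beat absolute change. A log-scale analysis also estimates a relative effect. The objection is therefore to an unadjusted ratio with a skewed baseline in the denominator, not to relative effects as such.

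**A reader might add that percentage change is meaningless for the continuous metabolic risk score.** That depends on how the score is centred. The article cites its formula without giving it, so nothing here rests on it.

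**Conclusion.** The point holds as an avoidable inefficiency and an undecided choice of scale, and it should be changed. It is not an error that invalidates the trial.

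On the natural reading, the stated analysis gives up 25%, 15% or 5% of variance at ρ of 0.5, 0.7 or 0.9. It leaves 50%, 30% or 10% of any chance baseline difference in the estimate. These figures assume equal variances at the two visits. The ratio is the same if only the 28 completers per arm are analysed.

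The two-scale problem does not depend on how the ambiguous phrase is read. In the assumed settings it matters little for a waist-like outcome (disagreement in 2–3% of runs) and noticeably for a skewed one (13–19%).

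**What to change.** Replace the sentence on change with one confirmatory analysis per continuous outcome: the difference between arms at t1 and at t2, from a model with the outcome's own baseline value as covariate. This can be ANCOVA, or a baseline term in the repeated-measures model already planned. Analyse triglycerides and their baseline on the log scale because of the expected skew, and report the back-transformed ratio. Keep percentage change, if wanted, as description without a p-value.

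Table 3 already schedules these outcomes at baseline, so no new data are needed. The cost is a wording change and one degree of freedom per model.

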##### Inclusion criteria

30 to 55 years-old.Having one or more risk factors for metabolic syndrome^1^ (waist circumference >94.5 cm for men and >89.5 cm for women; blood pressure ≥130/85 mmHg; triglycerides in plasma ≥150 mg/dL; HDLc in plasma <40 mg/dL for men and <50 mg/dL for women; fasting glycaemia ≥100 mg/dL).Low active (achieving less than 150 min/week of moderate-to-vigorous physical activity or to have not participated in any supervised exercise programmes for at least the last 24 weeks).Accept and sign written informed consent.Accept the randomized group assignment.

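### The intervention effect is defined on change from baseline, with no stated model that uses the baseline value as covariate; naming one would be a free gain in precision

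*Protocol article*

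**What the plan says.** Statistical methods in the Protocol article sets two time frames for the intervention effect: the end of the intervention (t1) and the 24-week follow-up (t2). It then defines the measure: "Change will be calculated as the change from baseline values, both as absolute values and as a percentage adjusted to baseline values". The longitudinal analysis is described in one sentence: "We will adjust repeated measures techniques to study the general behaviour of the outcomes in the follow-up". It does not say whether baseline enters that analysis as a covariate or as one of the responses. The reported effect size is also unadjusted as written: "Effect size will be estimated as the mean standardized difference between the mean of each group divided by the pooled standard deviation".

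Baseline differences between arms are tested by chi-square or Fisher's exact test and by ANOVA or Kruskal-Wallis, and then: "If significant differences are detected we will use Student’s *t*-test (or Mann–Whitney test) for each pair of groups". No consequence of these tests for the outcome analysis is given. ANOVA and t-tests are named only for this baseline comparison; the between-arm test of the intervention effect is not named. Missing values are filled by last observation carried forward (LOCF).

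**The concern.** The trial measures every main outcome at baseline, but the stated effect measure uses that value only by subtracting or dividing by it. Subtraction assumes that each unit of baseline difference persists in full to follow-up. When r is below 1 it does not. The change score then over-corrects for any chance imbalance and carries more noise than a model that estimates the slope on baseline. Dividing by baseline does not estimate that slope either.

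What is at stake is precision in a trial of about 35 per arm, and the sensitivity of each contrast to the imbalance that happens to arise. This weighs most where true differences are likely to be small. The hypothesis at the end of Background includes a comparison of two exercise arms that both receive the same counselling. The sample size section gives a power statement for waist circumference only.

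**Working it through.** **Inputs from the Sample size section.** Waist change of 6.0 cm, SD 5.3 cm (read as the SD of change), "a beta risk of 0.2 and an alpha risk of 0.05 when using a bilateral contrast", 20% drop-out, 35 per arm. Evaluable: 35 × 0.8 = 28 per arm.

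**The plan's own figure.** n per arm = 2 × (1.96 + 0.84)² × (5.3/6.0)² = 12.2, so 13; 13/0.8 = 16.3, so 17. The stated 35 per arm does not follow from these inputs. That is a separate matter; here it only fixes how many participants are available.

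**Assumed.** The article gives no r, so r = 0.5, 0.7 and 0.9 are used. SDs are taken as equal at both visits (s).

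**Step 1, variance.** Var(change) = 2(1-r)s². Var(ANCOVA residual) = (1-r²)s². Ratio = (1+r)/2. This ignores the small cost of estimating one slope.

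**Step 2, LOCF.** A missing t1 value is replaced by the baseline value, so that participant has zero change. If 20% of t1 values are filled this way (assumed), at random and with similar means at both visits, the correlation becomes r' = 0.8r + 0.2.

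| r | ratio (1+r)/2 | variance cut | r' under LOCF | variance cut under LOCF |
|---|---|---|---|---|
| 0.5 | 0.75 | 25% | 0.60 | 20% |
| 0.7 | 0.85 | 15% | 0.76 | 12% |
| 0.9 | 0.95 | 5% | 0.92 | 4% |

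**Step 3, power for waist.** 28 per arm, SD of change held at 5.3, ANCOVA SD = 5.3 × √((1+r)/2), normal approximation.

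| | change score | ANCOVA, r = 0.5 | r = 0.7 | r = 0.9 |
|---|---|---|---|---|
| SD used (cm) | 5.30 | 4.59 | 4.89 | 5.17 |
| Power, 6.0 cm | 98.9% | 99.8% | 99.6% | 99.2% |
| Power, 4 cm | 80.6% | 90.3% | 86.5% | 82.6% |
| Power, 3 cm | 56.3% | 68.6% | 63.2% | 58.4% |
| Detectable at 80% (cm) | 3.97 | 3.44 | 3.66 | 3.87 |

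The 4 cm and 3 cm rows are illustrations; the article states only 6.0 cm.

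**Step 4, imbalance.** Given an observed baseline difference D between two arms, the expected change-score contrast is the true effect minus (1-r)D. A one-standard-error D is s × √(2/28) = 0.267s, and the waist s implied by an SD of change of 5.3 is 5.3/√(2(1-r)).

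| r | implied s (cm) | one-SE imbalance (cm) | shift (cm) |
|---|---|---|---|
| 0.5 | 5.30 | 1.42 | 0.71 |
| 0.7 | 6.84 | 1.83 | 0.55 |
| 0.9 | 11.85 | 3.17 | 0.32 |

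**The case against.** The strongest reply is that the article never names the between-arm test. It says how change will be calculated, its own sentence speaks of adjusting to baseline, and it announces repeated-measures techniques that could involve baseline properly. It also condenses a fuller protocol, and an analysis plan may exist. This stands in part: it cannot be said that the trial will use no adjustment. But the phrase about adjustment is attached to the percentage, where scaling is the natural meaning, and nothing is attached to the absolute change. The article has also gone beyond leaving the matter open, because it commits to an effect measure, and a better use of the same data is available.

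A reader might infer that the repeated-measures analysis is only the change-score test again. With three arms and three visits the overall group-by-time test has (3-1) × (3-1) = 4 degrees of freedom, so it is not. Only a single contrast of t1 or t2 against an unconstrained baseline is a difference in change. A mixed model that holds baseline means equal across arms is essentially equivalent to ANCOVA. The article does not say which is meant.

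A reader might also infer that the results will be biased. Under randomisation the change-score contrast is unbiased on average; the shift in Step 4 is conditional on the imbalance observed.

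Nor does the entry rule ("Having one or more risk factors for metabolic syndrome") make things worse. Mixing normal and raised baselines widens the true spread, which for given measurement noise raises r and reduces what ANCOVA gains.

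Finally, the power figures use 28 completers, whereas the stated analysis keeps everyone with a baseline assessment (about 35 per arm) under LOCF. This objection stands: the gain is then smaller, as Step 2 shows.

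**Conclusion.** The point holds as a worthwhile free improvement, not as a flaw that undermines the trial. The stated effect measure is change from baseline, no baseline-covariate model is named, and the wording on adjustment is ambiguous.

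The gain from a covariate model is a variance reduction of 5% to 25% over assumed r of 0.9 to 0.5, or about 4% to 20% with 20% of t1 values carried forward. For the planned 6.0 cm waist difference it is immaterial, since power is about 99% either way. For a 4 cm difference with 28 completers per arm, power rises from 80.6% to between 82.6% and 90.3%. At r of 0.9 or more there is little to gain. These figures rest on an assumed r, equal SDs at both visits and, for waist, on reading 5.3 cm as the SD of change. That other outcomes have lower r is plausible but not shown in the article.

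**What to change.** In Statistical methods, state that between-arm differences at t1 and t2 are estimated by ANCOVA, or by one mixed model with arm-by-visit terms, on the t1 and t2 values with the baseline value of the same outcome as covariate. Say that the arm differences are read from that model. Keep absolute and percentage change as description only. If baseline adjustment was already intended, the same sentence removes the ambiguity.

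The cost is wording. The outcome schedule (Table 3) already has the main clinical, laboratory and questionnaire outcomes measured at baseline, t1 and t2, so no further data are needed.

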**Methods/Design:**

Three-arm, randomized controlled clinical trial implemented in the primary care setting, with a duration of 40 weeks (16 weeks intervention and 24-week follow-up).

Adults aged 30 to 55 years with metabolic risk factors will be randomized into three intervention groups: 1) aerobic interval training (16 supervised training lessons) plus a healthy lifestyle counselling programme (6 group and 3 individual meetings); 2) low-to-moderate intensity continuous training (16 supervised training lessons) plus the same counselling programme; or 3) the counselling- programme without any supervised physical exercise.

The main output variables assessed will be risk factors for metabolic syndrome (waist circumference, blood pressure, and levels of plasma triglycerides, high-density lipoproteins and glucose), systemic inflammation, cardiorespiratory fitness, physical activity and sedentary behaviour, dietary habits, health-related quality of life, self-efficacy and empowerment. Economic factors will also be analysed in order to determine the cost-effectiveness of the programme. These variables will be assessed three times during the study: at baseline, at the end of the intervention, and at follow-up. We estimate to recruit 35 participants per group.

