#### Cost analysis

Direct and indirect costs of setting up and running the interventions will be calculated in order to assess the economic aspect. HRQoL scores will be used to weight survival years and, thus, to generate QALYs (Quality Adjusted Life Years). The cost-effectiveness analysis will be conducted in accordance with the current practice methods for economic assessment [52]. The primary cost-effectiveness outcome will be a reduction in the metabolic risk score.

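### No primary efficacy endpoint, visit or change scale is named, and one unadjusted 5% level serves a set of five risk factors

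*Protocol article*

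**What the plan says.** - **Aim.** The abstract and the Background give the primary aim as managing metabolic syndrome risk factors in low-active adults. This is a set, and no member of it is singled out.
- **Main variables.** The abstract states "The main output variables assessed will be risk factors for metabolic syndrome" and lists five factors: waist circumference, blood pressure, triglycerides, HDL cholesterol and glucose. The same sentence adds inflammation, fitness, activity, diet, quality of life, self-efficacy and empowerment. The Background places most of these additions among the secondary aims.
- **Hypothesis.** The Background predicts that participants given vigorous supervised exercise "will present greater improvements in terms of metabolic risk, physical condition, physical activity/sedentary behaviours and psychological parameters at the end of the intervention". The same is predicted for the later follow-up visit, and the comparison is with the lower-intensity and counselling-only programmes. It gives no criterion for calling this supported.
- **Sample size.** The trial is sized "to detect a mean change in waist circumference of 6.0 cm (SD 5.3"), on waist circumference alone.
- **Composite.** A continuous risk score (cMSSy) built from the five factors is defined but not ranked. Under Cost analysis: "The primary cost-effectiveness outcome will be a reduction in the metabolic risk score".
- **Analysis.** Statistical methods labels t1 (16 weeks) as efficacy and t2 (24 weeks later) as durability. Change is to be computed as absolute values and as percentages, and repeated measures techniques are foreseen. For all analyses, "the level of significance will be set at" p < 0.05.

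**The concern.** A trial's false-positive rate is defined only once it is fixed which result counts as success. Here the aim names five variables and the sizing uses one of them. A composite of all five also exists, and nothing says which will decide the question. Two visits and two scales multiply the options. If any favourable factor, contrast, visit or scale may be put forward, the 5% level does not describe the error rate for the primary aim, and the choice can be made after the data are seen. The abstract reports retrospective registration, so clear prespecification in this article matters all the more.

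**Working it through.** **1. The plan's own figure.** Inputs from the Sample size section: a difference of 6.0 cm, SD 5.3, and "beta risk of 0.2 and an alpha risk of 0.05 when using a bilateral contrast". For two means, n per arm = 2 × (1.96 + 0.84)² × (5.3/6.0)² = 12.2, so 13. With 20% drop-out, 13/0.8 = 16.25, so 17 per arm and 51 in all. The plan states 105. The stated figure does not reproduce. That is a separate matter and does not decide this point. What matters here is that only waist circumference has planning values.

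**2. Arm size for the error calculation.** From "Assuming a 20% drop-out rate at follow-up, we aim to recruit 35 individuals for each intervention group": 35 × 0.8 = 28 completers per arm. The plan would carry last observations forward, so the analysed number could be nearer 35. With no true effect the error rates barely depend on this.

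**3. Number of possible tests.** Five factors × three pairwise contrasts × two visits = 30 on one scale. If each contrast is replaced by one three-arm omnibus test, there are 5 × 2 = 10.

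**4. Independence benchmark**, 1 − 0.95^k: k = 5 gives 22.6%, k = 10 gives 40.1%, k = 30 gives 78.5%. Contrasts share arms, and factors and visits are correlated, so these serve as upper benchmarks only.

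**5. Simulation with no true effect.** 28 per arm, one scale. The document gives no correlations, so these are assumed: 0 to 0.5 between factors and 0.5 to 0.8 between visits.

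| What counts as a positive result | Chance of at least one |
|---|---|
| Omnibus test per factor, t1 only (5 tests) | 19–24% |
| Omnibus test per factor, t1 and t2 (10 tests) | 28–39% |
| Result favouring interval training over either comparator, t1 | 16–21% |
| The same, t1 and t2 | 22–35% |
| Either interval-training contrast, two-sided, t1 (10 tests) | 32–40% |
| The same, t1 and t2 (20 tests) | 45–60% |
| All three pairwise contrasts, t1 and t2 (30 tests) | 56–71% |
| Interval training beats both comparators on the same factor and visit | 3–5% |

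**6. Adding percentage change as a second scale.** Over a wider set of assumptions (0–0.7 between factors, 0–0.9 between visits, 0.8–0.95 between scales) the ranges are 29–52% for 20 omnibus tests, 23–48% for a result favouring interval training, 55–84% for 60 pairwise tests, and 4–6% for beating both comparators.

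**7. The proposed rule.** For one endpoint at t1 on one scale, three unadjusted pairwise tests give about 12% (1 − 0.95³ = 14.3% if independent). A global three-arm test at 5%, followed by pairwise tests only if it is significant, gives about 5%. The reason is simple. If all three arms are equal, the global test guards the error. If they are not all equal, at most one pairwise null hypothesis can be true, and it is tested at 5%.

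**The case against.** Much can be said for the plan. This is a condensed article, and a multiplicity method, the list of contrasts and the model may properly sit in an analysis plan that is not shown. A hierarchy partly exists: there are primary and secondary aims, and t1 and t2 carry different labels. Pairwise tests are stated only for the baseline comparison after a significant omnibus test, so their use for the intervention effect is an inference. Nor does the plan say that both scales will be tested for every outcome. The hypothesis can fairly be read as requiring interval training to beat both comparators, and that rule keeps the error near 5%.

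These points stand, and they rule out two stronger readings that a reader might reach. One is that a false success is more likely than not. That holds for all 30 pairwise tests under the step 5 correlations, but that count includes continuous training against counselling and results in either direction. A false finding in favour of interval training is 16–35% on one scale, below one half. The other is that three sections name three rival lead outcomes. The risk score is called primary for cost-effectiveness only, and both it and waist circumference belong to the same five-factor set.

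The objection does not remove the gap itself. The primary endpoint defines the trial and should agree with the variable used for sizing, so it belongs in the protocol. The article has an aim, a sample-size section and an analysis section, and together they do not settle on one. It also states no rule that interval training must beat both comparators.

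**Conclusion.** The point holds in this form: no primary efficacy endpoint, visit or scale is fixed, the aim covers five factors while the sizing uses one, and a single unadjusted 5% level applies to all. If any one significant result may count, the error for the primary aim runs from about 16% to 71% on one scale, depending on the tests and the success rule. Only the rule of beating both comparators on the same measure keeps it at about 5% or less. The ranges rest on no true effect, 28 per arm and assumed correlations. The document does not fix which row of the table applies, so no single probability should be attached to the plan.

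**What to change.** Name one primary endpoint: the between-arm difference at t1 in absolute change in waist circumference, the variable on which the trial was sized. If the sponsor prefers the composite, cMSSy at t1 answers the stated aim more directly. An effect size and SD must then be given, because the document has none and power for it cannot be checked.

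Test the endpoint with one global three-arm test at 0.05 and, only if that is significant, the three pairwise contrasts at 0.05 each. Label the other factors, t2 and percentage change as secondary, reported with estimates and confidence intervals. Bring the abstract's list of main variables into line with the primary and secondary aims.

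The cost is about a paragraph. The other single factors can then no longer each be claimed as primary. No extra participants are implied if waist circumference is kept and the 6.0 cm is taken as a between-arm difference. Even a Bonferroni split over three pairs would need 17 completers per arm (17/0.8 = 21.25, so 22 recruited), against the planned 28 completers.
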